## Abstract

**Background:**

Periodontal disease (PD) is an infectious clinical entity characterized by the destruction of supporting tissues of the teeth as the result of a chronic inflammatory response in a susceptible host. It has been proposed that PD as subclinical infection may contribute to the etiology and to the pathogenesis of several systemic diseases including Atherosclerosis. A number of epidemiological studies link periodontal disease/edentulism as independent risk factor for acute myocardial infarction, peripheral vascular disease, and cerebrovascular disease. Moreover, new randomized controlled clinical trials have shown an improvement on cardiovascular surrogate markers (endothelial function, sICAM, hsPCR level, fibrinogen) after periodontal treatment. Nonetheless, such trials are still limited in terms of external validity, periodontal treatment strategies, CONSORT-based design and results consistency/extrapolation. The current study is designed to evaluate if periodontal treatment with scaling and root planning plus local delivered chlorhexidine improves endothelial function and other biomarkers of cardiovascular disease in subjects with moderate to severe periodontitis.

**Methods/Design:**

This randomized, single-blind clinical trial will be performed at two health centers and will include two periodontal treatment strategies. After medical/periodontal screening, a baseline endothelium-dependent brachial artery flow-mediated dilatation (FMD) and other systemic surrogate markers will be obtained from all recruited subjects. Patients then will be randomized to receive either supragingival/subgingival plaque cleaning and calculus removal plus chlorhexidine (treatment group) or supragingival plaque removal only (control group). A second and third FMD will be obtained after 24 hours and 12 weeks in both treatment arms. Each group will consist of 49 patients (n = 98) and all patients will be followed-up for secondary outcomes and will be monitored through a coordinating center. The primary outcomes are FMD differences baseline, 24 hours and 3 months after treatment. The secondary outcomes are differences in C-reactive protein (hs-CRP), glucose serum levels, blood lipid profile, and HOMA index.

**Discussion:**

This RCT is expected to provide more evidence on the effects of different periodontal treatment modalities on FMD values, as well as to correlate such findings with different surrogate markers of systemic inflammation with cardiovascular effects.

**Trial registration number:**

ClinicalTrials.gov Identifier: NCT00681564.

## Background

Cardiovascular disease continues to be the main cause of morbidity and mortality worldwide. Despite the existence of novel therapeutic approaches designed for the prevention and treatment of atherosclerosis, the number of deaths associated to cardiovascular events remains constant in most countries[1]. For instance, in Colombia, one out of five deaths can be attributed to ischemic cardiovascular disease[2]. During the last decade it has been widely accepted that inflammation plays a key role in the development of atherosclerosis. Multiple epidemiological studies have confirmed the association between high levels of acute phase reactants such as C-reactive protein (CRP), fibrinogen, Serum Amyloid A and soluble adhesion molecules like ICAM-1, E-Selectin, VCAM-1 with the progression of atherosclerosis and also with an increased risk for cardiovascular disease[3].

New scientific evidence from the last two decades including epidemiological, *in vivo *and *in vitro *assays supports the notion that the immune system significantly contributes in the development and progression of atherosclerosis[4]. This new theory proposes that any potential noxious challenge to the host immune response could be related to the pathogenesis of atherosclerosis[5]. Hence, other nontraditional risk factors for cardiovascular events, such as infections and rheumatologic autoimmune diseases have emerged as important risk factors[6].

Several epidemiological studies have also suggested that periodontal infection is an independent risk factor for acute myocardial infarction, peripheral vascular disease and cerebrovascular disease. A recent meta-analysis on the subset of five cohort studies (86,092 patients, follow-up > 6 years) found increased incidence of coronary heart disease (RR = 1.24, 95% CI 1.14-1.36, p < .0001) in patients with less than 10 teeth. In the subset of cross-sectional studies at the same meta-analysis report, prevalence of coronary heart disease was reported to be significantly high (OR = 1.59, 95% CI 1.329-1.907, p < .001)[7]. The association between periodontitis and cardiovascular disease in meta-analysis literature is stronger when systemic inflammatory and serologic markers are used to determine the systemic bacterial exposure secondary to periodontitis[8].

Several biological mechanisms have been suggested to explain the association between periodontal infections and atherosclerosis:

### 1. Systemic consequences of periodontal infection (indirect pathway)

Patients with periodontitis have increased levels of C-reactive protein, fibrinogen, TNF-α, IL-1, IL-6 and other acute phase reactants associated to cardiovascular events[9,10]. Proinflammatory cytokines (TNF-α, IL-1, IL-6) reduce the expression of endothelial Nitric Oxide Synthase (eNOS),[11,12] increase endothelial synthesis of NADPH oxidase,[13] and promotes the expression of endothelial cell adhesion molecules (e-Selectin, ICAM-1, VCAM-1)[14]. It is well-know that the absence of anti-atherogenic properties in the endothelium augments the vascular migration of leukocytes (diapedesis) to atherosclerotic plaques[4]. In addition, increased activation of platelets has been reported in subjects with periodontitis[15]. Despite the evidence, the contribution to other classic risk factors of CVD of the systemic inflammation associated with periodontitis remains largely unknown.

### 2. Invasion of periodontal pathogens into atherosclerotic plaques (Direct pathway)

Periodontal pathogens (*i.e., Porphyromonas gingivalis, Aggregatibacter actinomycetencomitans, Prevotella intermedia, Treponema denticola*, and *Eikenella corrodens*) have been found in atherosclerotic plaques[16,17]. Recent studies have shown that invasion by *P. gingivalis *induces the expression of endothelial cell adhesion molecules, IL-8, IL-6, MCP-1, and TLR-4[18-20]. *P. gingivalis *HSP60 (GroEL) induces TLR-2 and TLR-4 expression on the surface of endothelial cells,[21] suggesting that autoimmune mechanisms secondary to periodontal infections could play a role in the progression and development of atherosclerosis[22].

Randomized controlled trials (RCTs) are therefore important to study the impact of periodontal infections on cardiovascular disease. A growing number of clinical trials designed to study the effects of periodontal treatment on cardiovascular disease have been published during the last decade[23-27]. All RCTs evaluating conventional periodontal therapy effects have used different biomarkers of inflammation and endothelial function as surrogate outcomes for cardiovascular events, whereas definitive endpoints such as death, ischemic heart disease and cerebrovascular accident are not frequently used. For instance, clinical trials with definitive cardiovascular endpoints in periodontitis patients are not available due to methodological limitations (*i.e. *larger sample sizes, or long term follow-up) and/or ethical aspects concerning the non-treatment of subjects with periodontitis for long periods of time.

Hence, the use of surrogate biomarkers in RCT evaluating the effects of periodontal treatment in the prevention of cardiovascular disease is justified, because the otherwise more definitive outcomes such as cardiovascular events, cardiovascular deaths, and hospitalizations for cardiovascular complications requires long follow-up periods. Surrogate biomarkers such as flow-mediated, endothelium dependent vasodilatation of the brachial artery (FMD) is a non-invasive, reproducible and easy technique for measuring endothelial function in humans[28]. FMD is decreased in subjects with cardiovascular risk factors (i.e. diabetes, hypertension, obesity, and smoking among others) and atherosclerosis[29]. Furthermore, positive changes in lifestyle (diet, smoking cessation and physical exercise) as well as cardiovascular drugs (ACE inhibitors, statins, oral hypoglycemic drugs, and calcium antagonists) improve endothelial function in humans[30-32]. The use of FMD as a biomarker for cardiovascular disease has been recently supported by studies reporting association between endothelial dysfunction and cardiovascular events[33].

To date, there are some published RCTs that have found an improvement on endothelial function after periodontal treatment (REF). However, there are several reasons to justify the development of more clinical trials to study this association:

1. Extrapolation of results to the general community (external validity): Only subjects with chronic severe generalized periodontitis (less than 1% of the adult population) have been included in clinical trials of periodontal treatment and endothelial function,[23-27] therefore there is no available evidence that periodontal treatment improves endothelial function in subjects affected by slight or moderate periodontitis, both more prevalent forms of periodontal disease. Furthermore, the effects of periodontal treatment on endothelial function in diverse ethnic/social groups with other co-morbidities (*i.e. *obesity, diabetes, cardiovascular disease, metabolic syndrome, chronic renal failure) are unknown.

2. Differences in periodontal disease treatment strategies: some treatment protocols of periodontal disease used in some RCTs are not available or affordable in non-industrialized countries (*i.e. *local antibiotic therapy with minocycline microspheres).

3. Methodological limitations of published trials: most published trials do not include a control group (single arm clinical trials) and only one RCT published to date by Tonnetti et al.[25] fully complied with the CONSORT statement[34]. Moreover, information regarding the periodontal diagnosis and disease parameters of the subjects included in recent clinical trials is frequently incomplete.

4. Consistency: results are consistent when the association persists despite the use of alternative designs, by different researchers and different geographic locations. More RCTs with design improvements and conducted by different research groups are required to confirm the beneficial effects of periodontal treatment on biomarkers of cardiovascular disease.

In summary, current evidence supports a biologically plausible association between periodontal disease and atherosclerosis. To date, few studies have evaluated the effects of periodontal treatment on endothelium-dependent brachial artery flow-mediated dilatation. Moreover, the evidence obtained from observational studies is still controversial, probably due to selection biases that have resulted in weaker association strengths. This RCT will be conducted to help to confirm a possible association between periodontitis and cardiovascular disease, to unveil some biological mechanisms by which periodontal treatment could reduce cardiovascular risk and to increase the external validity of previous studies.

The study hypothesis is that periodontal treatment with scaling and root planning supplemented with chlorhexidine (Full-Mouth Disinfection) - without systemic antibiotics, improves endothelial function and other biomarkers of cardiovascular disease in subjects with moderate to severe periodontitis. **ClinicalTrials.gov Identifier: NCT00681564**.

**Exclusion Criteria**

• History of antibiotic use in the previous three months
• Pregnant or lactating females
• Treatment with antihypertensive, antilipemic, antiarrhythmic, and other cardiovascular drugs
• Systemic diseases such as diabetes, HIV/AIDS, liver disease, chronic renal failure, tuberculosis, and autoimmune diseases
• Previous history of cardiovascular disease: Acute myocardial infarct, stable angina, unstable angina, heart failure, atrial fibrillation, AV blockade, peripheral vascular disease, and cerebrovascular accident
• Patients who received periodontal treatment within the last 6 months
• Patients who require antibiotic prophylaxis before examination or treatment
• Patients with some mental disability

### Settings

Treatments and tests (blood samples, endothelium-dependent brachial artery flow-mediated dilatation, radiographs, subgingival samples and microbial cultures) of this RCT will be performed at the Universidad del Valle at Cali, Colombia. Patients will be recruited from *State-funded primary care Health Centers *(Cañaveralejo and Siloe), and Universidad del Valle dental school, located in the same geographical region of Cali.

### Study design

This is a single blind (evaluators of study variables and outcomes) clinical trial designed to evaluate the effects of periodontal treatment on endothelium-dependent brachial artery flow-mediated dilatation in 98 subjects with moderate to severe periodontitis. Eligible subjects for the present study will be invited to the following visits (Figure 1):

**Figure 1 F1:**
[figure not shown]

#### - Visit I

periodontal clinical parameters, subgingival samples collection (for microbial cultures and Polymerase Chain Reactions to detect specific periodontal pathogens), periapical radiographs, medical examination, and structured interview at the School of Dentistry (Universidad del Valle).

#### - Visit II

baseline endothelium-dependent brachial artery flow-mediated dilatation and anthropometric parameters (weight, height, and abdominal circumference). A fasting blood sample will be obtained to determine glucose, insulin, hs-CRP, lipid profile, and a pro-inflammatory cytokine panel by Multiplex^®^.

#### - Visit III

randomization to supragingival and subgingival plaque cleaning and calculus removal, four quadrants in one session, plus chlorhexidine (treatment group, full-mouth disinfection protocol) or supragingival plaque removal (control group, adult prophylaxis). All the interventions will be performed by two qualified periodontists at the School of Dentistry (Universidad del Valle), at Cañaveralejo Health Center or at Siloe Health Center.

#### - Visit IV (24 hours after periodontal treatment)

endothelium-dependent brachial artery flow-mediated dilatation and fasting blood samples at the School of Basic Sciences (Universidad del Valle).

#### - Visit V (12 weeks after periodontal treatment)

endothelium-dependent brachial artery flow-mediated dilatation, periodontal parameters, and subgingival samples at the School of Basic Sciences at the Universidad del Valle. A fasting blood sample will be obtained to determine glucose, insulin, hs-CRP, lipid profile, and cytokines by Multiplex^®^.

#### - Visit VI

follow-up (intervention group) and treatment (control group) performed by a periodontist at the School of Dentistry (Universidad del Valle), Cañaveralejo or Siloe.

### Outcomes

#### - Primary outcome

The primary outcome is the difference on endothelium-dependent brachial artery flow-mediated dilatation (FMD) at baseline and three months after randomization [Time Frame: Baseline, 24 h, and 12 weeks after treatment].

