### Sample size

The primary outcome FMD was selected as the critical variable to calculate the sample size. 49 patients (98 in total) in each group are required to have an 80% chance of detecting as significant (at the two sided 5% level) a 1% difference between the two groups in the mean FMD, with assumed standard deviation of 2.6 and a planned 15% rate of missing patients on the follow up.

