### Statistical analysis

All statistical analyses will be performed using the intention-to-treat principle unless stated otherwise. A P of 0.05 will be used as a cutoff for statistical significance. The primary outcome (difference on endothelium-dependent brachial artery FMD at baseline and three months after randomization) and the secondary outcome (hs-CRP, glucose, blood lipid profile, and HOMA index) will be analyzed using repeated measures ANOVA for continuous variables. Differences in proportions in outcomes between the treated group and the control group will tested for statistical significance by χ2-test or Fisher exact test if applicable.

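### The abstract makes both 24-hour and 3-month FMD primary while the body names only 3 months; if all three times enter the repeated measures ANOVA, the omnibus test does not isolate the 12-week effect

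*Protocol article*

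**What the plan says.** The protocol article describes the primary outcome in three places.

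- **Abstract, Methods/Design** (plural): "The primary outcomes are FMD differences baseline, 24 hours and 3 months after treatment". It also confirms the measurements: "A second and third FMD will be obtained after 24 hours and 12 weeks in both treatment arms".
- **Outcomes, Primary outcome** (singular): "The primary outcome is the difference on endothelium-dependent brachial artery flow-mediated dilatation (FMD) at baseline and three months after randomization". The bracket that follows adds 24 h: "Time Frame: Baseline, 24 h, and 12 weeks after treatment".
- **Statistical analysis** (singular, 24 h not mentioned): "difference on endothelium-dependent brachial artery FMD at baseline and three months after randomization". This outcome "will be analyzed using repeated measures ANOVA for continuous variables". The threshold is general: "A P of 0.05 will be used as a cutoff for statistical significance".

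The Sample size section powers one between-group difference in mean FMD "at the two sided 5% level" and does not say at which visit. No section ranks 12 weeks above 24 h.

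**The concern.** A reader cannot tell whether 24-hour FMD is a primary outcome. The abstract says it is. The Outcomes sentence and the Statistical analysis section say it is not, and the time frame in the Outcomes section leaves the matter open.

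The named analysis does not settle it. With three time points, the group-by-time F test asks whether the arms' profiles differ in any way over time. It responds to a difference at 24 h as readily as to one at 12 weeks, and it has no direction. A short-lived difference is plausible here. The Interventions section contrasts a full-mouth scaling and root planing session under local anaesthesia with a supragingival cleaning, and Visit IV measures FMD one day later.

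What is at stake is what the primary p-value means. It could be significant because of a transient 24-hour change with no 12-week effect. On the abstract's plural wording, two separate tests at 0.05 would each offer a route to significance.

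**Working it through.** The plan gives no error rate of its own for this point, so there is no stated figure to reproduce. The stated sample size is taken as given; whether it follows from its inputs is a separate matter.

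**Inputs from the document.** 49 per arm, 15% loss, SD 2.6, difference of 1 FMD percentage point, two-sided 5% (Sample size). FMD at baseline, 24 h and 12 weeks (abstract; Visits II, IV and V). Completers per arm: 49 × 0.85 = 41.65, taken as n = 42.

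**Assumptions.** The SD of 2.6 is that of a single FMD value. Within-patient correlation ρ is the same for every pair of times and is 0.3, 0.5 or 0.7. The document gives no correlation.

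**1. Three times in the ANOVA, effect at 24 h only.**

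- The arm differences are (0, 1, 0). Centred on their mean they are (−1/3, 2/3, −1/3), with sum of squares 2/3.
- Noncentrality of the group-by-time test: λ = (n/2) × (2/3) / [SD² × (1 − ρ)] = 14 / [6.76 × (1 − ρ)].
- Degrees of freedom: 2 and 2 × (84 − 2) = 164. The 5% critical value of F is 3.05.

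| ρ | λ | P(significant), n = 42 | Same, n = 49 |
|---|---|---|---|
| 0.3 | 14 / 4.732 = 2.96 | 31% | 36% |
| 0.5 | 14 / 3.380 = 4.14 | 42% | 48% |
| 0.7 | 14 / 2.028 = 6.90 | 64% | 71% |

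A simulation of 4,000 trials per scenario agrees: 30%, 41% and 63% with n = 42. In the same simulated trials, the between-arm test of the 12-week change was significant in 5.1%, 4.9% and 4.8%, which is its nominal level.

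The sign of the difference drops out of λ. A 1-point fall at 24 h gave 32%, 42% and 65% in the simulation.

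**2. Two times in the ANOVA, baseline and 12 weeks.** The group-by-time F test has 1 numerator degree of freedom. It equals the square of the two-sample t statistic on each patient's 12-week change. A 24-hour effect cannot influence it, and it tests the stated outcome exactly.

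**3. 24 h and 12 weeks as two primaries, each at 0.05.** With no true effect, the family-wise error is 1 − P(|Z₁| < 1.96 and |Z₂| < 1.96).

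- Independent tests: 1 − 0.95² = 9.75%.
- Correlation 0.5 between the two statistics: 9.1%. This is the value for two changes from a shared baseline under the model above: covariance SD²(1 − ρ), each variance 2 × SD²(1 − ρ), ratio 0.5.
- Correlation 0.8: 7.8%.

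The simulated range under no effect was 8.0% to 9.4%.

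**The case against.** The strongest reply is that the body of the article is more consistent than it looks. Outcomes and Statistical analysis both define a singular outcome from baseline to three months. The bracketed time frame can be read as a measurement schedule, since almost the same bracket follows the secondary outcomes. Read literally, the Statistical analysis section analyses only baseline and three months, and step 2 then applies. This stands as a possible reading. But that section does not limit the times entered, it applies the same ANOVA to secondary outcomes collected at all three times, and the abstract conflicts with it on any reading.

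A second reply is that the choice of ANOVA term, contrast and alpha rule commonly sits in a full protocol or analysis plan that is not shown. That is fair, and the absence of those details is not the point here. The point is that the article defines its primary outcome in two ways that cannot both hold.

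Three stronger inferences are tempting and not supported:

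- *The ANOVA cannot isolate the 12-week effect.* This is true only if 24 h is entered.
- *The trial could be declared a success on a 24-hour worsening.* The rates above are rates of statistical significance. The hypothesis at the end of the Background is that treatment improves endothelial function, and no section says that significance in either direction counts as success. That hypothesis also names no time point, so a test cannot be faulted for missing a 3-month hypothesis.
- *The group main effect is a weak primary test because it averages in the pre-treatment value.* No section proposes the main effect as the primary test.

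**Conclusion.** The point holds in a conditional form. The contradiction between the abstract and the body over whether 24-hour FMD is primary is on the page and depends on no assumption.

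Its consequence depends on how the analysis is run. With all three times in the ANOVA, as the abstract and the Outcomes time frame suggest, a 1-point effect confined to 24 h gives a significant group-by-time test in about 31% to 64% of trials at 42 per arm, against 5% for a 12-week contrast. That range rests on an SD of 2.6 for single values, equal correlations between times and an assumed ρ of 0.3 to 0.7. With two primaries each at 0.05, the family-wise error is about 8 to 10%. With only baseline and 12 weeks entered, neither problem arises.

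The article does not say which of these applies, and the answer decides what the primary p-value shows.

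**What to change.** Align the abstract, Outcomes, Sample size and Statistical analysis sections on one primary outcome: the between-arm difference in FMD at 12 weeks, preferably adjusted for the baseline FMD already collected. Test it as a single two-sided contrast at 0.05. State that the primary p-value comes from this contrast and not from an omnibus F test. The repeated measures model can stay as the framework for estimating it. Report 24-hour FMD as a secondary outcome, with its direction and confidence interval.

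Keeping both times as primary, with a stated rule for sharing alpha, would also remove the contradiction. The Sample size section would then have to cover two comparisons.

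The cost is small. No visit, measurement or patient is added. The wording changes in four places, the source of the primary p-value is fixed, and the sponsor gives up a success claim based on 24-hour FMD alone.
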